## Data collection and management

### Plans for assessment and collection of outcomes {18a}

The following data will be recorded upon inclusion in the trial: demographics, medical history, tumour characteristics, treatment characteristics, and dosimetric parameters. During radiation treatment and follow-up, acute toxicity will be assessed as mentioned above (CRO, PRO, objective assessment, and PRE).

### Plans to promote participant retention and complete follow-up {18b}

Patients are seen daily during radiation treatment. Upon withdrawal of informed consent, the reason will be recorded and data available until this point in time will be used for analysis.

### Data management {19}

All data recorded during the trial will be pseudonymised, with patients being identifiable by a unique patient number. The identification list will be stored on a password-protected secure server. Data will be collected on trial-specific documentation sheets, signed and dated by the assessing radiation oncologist for every separate patient visit. All data will be transferred into a single database (electronic case report form). All trial documents will be securely stored for 10 years.

### Confidentiality {27}

All data will be handled according to the General Data Protection Regulation (GDPR), ensuring strict confidentiality.

### Biological specimens {33}

Not applicable.

#### Statistical methods

### Statistical methods for primary and secondary outcomes {20a}

Mean, median, SD, and range will be calculated for all applicable clinical data. Differences in baseline patient characteristics between both treatment arms will be assessed with Pearson’s *χ*^*2*^ or Student’s unpaired *t* test, as appropriate. The primary endpoint will be assessed using the Mann–Whitney-Wilcoxon test, and an odds ratio (with a 95% confidence interval) will be calculated for the occurrence of grade ≥ 2 RD. For the pairwise comparison of categorical variables (clinician- and patient-reported outcomes) between treatment groups, the Mann–Whitney-Wilcoxon test will be performed. The comparison of continuous variables (spectrophotometric readings) will be performed with Student’s unpaired *t* test (after proving homoscedasticity with Levene’s test). The statistical significance level will be defined as *p* < 0.05.

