### Sample size {14}

The primary endpoint of this trial is clinician-assessed RD (as per CTCAE v5.0) in the NIPP and placebo group upon radiation treatment completion. The sample size calculation is based on the results of our phase 2 trial [28]. A decrease in mean clinician-reported RD severity upon radiation treatment completion of at least one third will be assumed with NIPP (RD severity with standard skin care: 1.06 ± 0.71 [4]). To detect such a difference (*Δ* = 0.35; standard deviation [SD] = 0.7) with 80% statistical power with a two-tailed *t*-test at a significance level of 5%, an analysed sample size of *n* = 128 is needed (i.e. 64 patients per treatment arm). We plan to analyse the CTCAE severity grades as ordinal data using a non-parametric Mann–Whitney-Wilcoxon test. The required sample size is, however, computed for a parametric test. In order to achieve the same degree of confidence as a similar parametric test, a larger sample size is thus needed for the non-parametric test [36]. As a rule of thumb, sample size will therefore be increased by an additional 10%, resulting in *n* = 140 (i.e. 70 patients per treatment arm). Based on both previous trials, we expect 20% drop-out after initial informed consent (*n* = 168 randomised). Of all patients being referred to our department, we expect 20% meeting inclusion criteria but declining participation (*n* = 202 enrolled and assessed for eligibility).

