#### Assignment of interventions: allocation

### Sequence generation {16a}

Using intrapatient randomisation (the irradiated breast is divided into a lateral and medial half; one breast half receives experimental treatment, while the other breast half receives standard of care or placebo) has proven useful in several trials investigating (acute or chronic) RD management approaches [37–40]. This omits the need for stratification based on known risk factors influencing the RD risk and limits confounding when assessing trial endpoints. The volatile nature of NIPP, however, does not allow such trial design, as potential diffusion to the contralateral (placebo) breast half with a subsequent effect is likely, as was the case in our phase 2 trial [28]. Therefore, a separate control group receiving standard skin care + placebo will be recruited. A 1:1 randomisation (NIPP:placebo) will be undertaken, with patient stratification based on two proven risk factors for RD development and severity: total radiation dose (i.e. presence or absence of a boost to the tumour bed) and irradiated breast volume (as measured in the radiation treatment planning computer tomography: small < 400 mL, medium 400 − 800 mL, large > 800 mL) [35, 41]. Patients will be assigned to intervention or placebo using a stratified block randomisation process (block size will be disclosed upon final publication of the results), using a computer-generated random number list, created by a team member not involved in the clinical part of the trial. Other factors which are known to modulate the RD risk (e.g. body mass index, diabetes mellitus, smoking history, Fitzpatrick skin type) will not be included in the stratification process, but will be documented and presented (including balance between groups).

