### Methods for additional analyses {20b}

Not applicable.

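### The primary Mann–Whitney test ignores the boost and breast-volume strata used in randomisation, so it is conservative and gives up power

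*Protocol article*

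**What the plan says.** **Allocation** (Protocol article, Sequence generation {16a}). "Patients will be assigned to intervention or placebo using a stratified block randomisation process". The stated basis is "patient stratification based on two proven risk factors for RD development and severity". The first factor is whether a tumour-bed boost is given. The second is breast volume on the planning CT, in three classes: "small < 400 mL, medium 400 − 800 mL, large > 800 mL". That makes 2 × 3 = 6 strata. The block size is withheld until publication.

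**Primary analysis** (Statistical methods for primary and secondary outcomes {20a}). "The primary endpoint will be assessed using the Mann–Whitney-Wilcoxon test". The Sample size section {14} says the same: "We plan to analyse the CTCAE severity grades as ordinal data using a non-parametric Mann–Whitney-Wilcoxon test". Neither place mentions the strata. The same section {20a} plans an odds ratio with a 95% confidence interval for grade ≥ 2 dermatitis and Mann–Whitney comparisons of the other clinician- and patient-reported outcomes, again with no adjustment stated.

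**Other analyses.** The section on additional analyses {20b} is marked as not applicable. Nothing elsewhere in the article uses the stratification factors in an analysis.

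**The concern.** The design and the test do not match. Under blocked allocation within strata the arms are nearly balanced on boost and volume, so chance imbalance in these factors contributes almost nothing to the arm difference. The unstratified Mann–Whitney test computes its null variance as if patients had been allocated without strata, so that variance still contains the between-stratum part. If the strata predict grade, the test's variance is too large, the real type I error is below the nominal 5%, and power is lower than the design could give.

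The loss grows with the prognostic strength that the protocol gives as its reason for stratifying. At stake is a higher chance of missing a true effect than 140 analysed patients need leave. The primary test is named in two sections, so this is a stated choice and not a detail left to a later document.

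**Working it through.** **1. The plan's own sample size.** Δ = 0.35 and SD = 0.7 give a standardised effect of 0.5. A two-sided t-test at 5% with 80% power needs 63.8 per arm, rounded up to 64, so 128 in total (power 80.1%). Adding 10% gives 128 × 1.10 = 140.8, against the stated 140. The figures reproduce. They assume no stratification.

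**2. Why the test is conservative.** The test divides W − E(W) by √V, where V = n₁n₀/[N(N−1)] · Σ(rᵢ − r̄)² over all N patients. With blocking inside strata, only the within-stratum part of that sum contributes to the real variance of W. That is roughly (1 − R²)V, where R² is the share of rank variance explained by the strata. The real type I error is then about

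2·[1 − Φ(1.96/√(1 − R²))].

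- R² = 0.11: 1.96/√0.89 = 2.08, so 3.8%
- R² = 0.13: 1.96/√0.87 = 2.10, so 3.6%
- R² = 0.19: 1.96/√0.81 = 2.18, so 2.9%
- R² = 0.22: 1.96/√0.78 = 2.22, so 2.6%
- R² = 0.29: 1.96/√0.71 = 2.33, so 2.0%

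**3. Simulation inputs.**
- From the article: control mean 1.06, SD 0.71; Δ = 0.35, so the NIPP mean is 1.06 − 0.35 = 0.71; two-sided 5%; N = 140; six strata.
- Assumed: blocks of 4; 2% grade 3; the prognostic strength of the strata, varied over a range.
- Control proportions: with p₃ = 0.02, p₁ + 2p₂ = 1.06 − 0.06 = 1.00 and p₁ + 4p₂ = 0.71² + 1.06² − 0.18 = 1.4477. Hence p₂ = 0.224, p₁ = 0.552 and p₀ = 0.204.

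**4. Results, unstratified against stratified (van Elteren).** Three simulations were run with different stratum structures. All used tie-corrected statistics.

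*Latent normal severity; boost 50/50, volume classes 20/40/40%; 6,000 null and 4,000 alternative runs:*

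| Latent variance explained | Type I error | Power |
|---|---|---|
| 0% | 4.5% vs 4.7% | 84.6% vs 83.9% |
| 5% | 4.4% vs 4.8% | 84.8% vs 85.4% |
| 10% | 4.0% vs 4.9% | 86.1% vs 87.1% |
| 20% | 3.8% vs 5.6% | 86.3% vs 90.1% |
| 30% | 2.3% vs 4.6% | 87.7% vs 92.8% |
| 40% | 1.8% vs 4.8% | 87.6% vs 94.7% |

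Simulation error is about 0.3 points for type I error and 0.5 points for power. The 5.6% is about two simulation errors above 5%.

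*Latent logistic severity, additive boost and volume effects, 6,000 runs; share of observed grade variance:*
- 0%: power 83.6% vs 83.4%
- 13%: type I error 3.3% vs 4.8%; power 86% vs 89%
- 22%: type I error 2.6% vs 4.9%; power 88% vs 93%

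*Uneven strata; share of observed grade variance 0%, 11%, 19%, 29%:*
- Type I error 4.9%, 4.0%, 3.1%, 2.2% unstratified; about 5% stratified
- Power 85%, 86%, 87%, 88% unstratified; 85%, 89%, 92%, 94% stratified
- The same pattern holds with 168 randomised and one sixth lost (168 × 5/6 = 140 analysed)

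The simulated unstratified type I errors in the last two sets (4.0%, 3.3%, 3.1%, 2.6%, 2.2%) lie close to the formula in step 2 (3.8%, 3.6%, 2.9%, 2.6%, 2.0%).

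**The case against.** The strongest reply is that nothing is invalid. The error is on the safe side, false positives are not inflated, and the planned test stays above the planned 80% power in every N = 140 setting simulated. Its power even rises as the strata become more prognostic. The loss exists only relative to a better test. All of this is correct, and it keeps the point an efficiency matter.

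Second, the size rests on a figure the article does not give. Calling the factors proven supports an association, not its strength. At 5% or less of latent variance the gain is under one power point, at 10% about one point, and at 0% the stratified test gains nothing. This also stands: the direction is certain, the magnitude is a range.

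Third, only rank tests were simulated. The confidence interval for the grade ≥ 2 odds ratio, the proportional-odds alternative and the secondary outcomes were not, so no figures are claimed for them.

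Fourth, sparse strata and drop-out might erode the gain. That does not stand: uneven strata, and 168 randomised with one sixth lost, gave the same pattern.

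Finally, the not-applicable entry under additional analyses is weak evidence in a condensed article, since an adjusted sensitivity analysis could sit elsewhere. That is fair, but the point does not need it. The primary test itself is named, twice, without the strata.

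**Conclusion.** The concern holds. The trial randomises by two factors because they are prognostic and then names a primary test that ignores them. The consequence is a conservative test and forgone power, not bias or inflated type I error. Against a van Elteren test on the same 140 patients, the forgone power is about nil if the strata explain nothing, roughly 3 points at 11–13% of grade variance, 5 at 19–22% and 6 at 29%. Type I error falls to between about 4% and 2% over that range. At 29%, the chance of missing the assumed effect is 12% with the planned test and 6% with the stratified one.

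These figures assume blocks of 4, 2% grade 3 in controls and the article's means and SD. The prognostic strength of the strata is unknown and drives the result. The change should be made, because it costs at most a fraction of a power point if the strata turn out not to matter.

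**What to change.** Before unblinding, amend the statistical methods section {20a} and the matching sentence in the sample size section {14}:

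- **Primary test:** a stratified Wilcoxon (van Elteren) test over the six randomisation strata, or a proportional-odds model of CTCAE grade on arm with boost and breast-volume class as covariates. Name one as primary. The van Elteren test is closest to the present plan; the model gives an effect estimate, but adds the proportional-odds assumption and estimates an odds ratio conditional on the covariates.
- **Strata:** use the values recorded at randomisation, and state in advance how very small strata will be pooled.
- **Other outcomes:** use the same factors for the secondary clinician- and patient-reported comparisons and for the grade ≥ 2 odds ratio.
- **Sensitivity analysis:** keep the unstratified Mann–Whitney test.

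No new data or patients are needed, since both factors are already known at randomisation. The sample size need not change. The cost is a protocol amendment, which under section {25} means Institutional Review Board approval, notice to the funder and trial staff, and a registry update. The article states that analysts and statisticians are blinded and that no interim analysis is planned, so the change can still be made cleanly. After unblinding it would look post hoc.

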### Interim analyses {21b}

There are no planned interim analyses. The excellent safety profile of NIPP renders an interim safety analysis or stopping rules obsolete. The efficacy of the intervention versus placebo will only be assessed if the preplanned sample size has been reached.

### Methods for additional analyses {20b}

Not applicable.

### Methods in analysis to handle protocol non-adherence {20c}

All analyses will be modified intention-to-treat, excluding participants not initiating allocated treatment. A secondary per protocol analysis will be performed as well.

### Plans to give access to the full protocol, participant-level data, and statistical code {31c}

Not applicable.

#### Oversight and monitoring

### Composition of the coordinating center and trial steering committee {5d}

The coordinating center consists of the principal investigator, investigators (all with full delegation), and the involved study nurses. Investigators will recruit and enroll patients in addition to performing the blinded outcome assessments. The unblinded study nurses will perform the administration of the allocated treatment. Five prescheduled investigator meetings are planned during the recruitment period to evaluate progress of the trial or assess any issues that might have arisen.

### Composition of the data monitoring committee {21a}

Data management and monitoring will be performed by a clinical research associate of the Studienzentrale Bonn (SZB), following the monitoring manual designed for this trial, to ensure reliability of trial results.

### Adverse event reporting and harms {22}

Not applicable. In both initial trials, no adverse events were reported, in line with previous trials using NIPP for other skin disorders, confirming the complete absence of side effects.

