Recent evidence has identified the skin microbiome as a risk factor for (severe) RD, postulating the hypothesis that bacterial decolonisation might be an effective prophylactic approach, which would be the main mode of action of NIPP in this context [21–23]. Furthermore, NIPP promotes proliferation and migration of keratinocytes, fibroblasts, and endothelial cells, thus facilitating tissue regeneration [24]. The expression of wound healing gene signatures alongside significant changes to the human skin barrier lipid stoichiometry are two additional modes of action, which are thought to positively impact the complex pathophysiology of RD [25, 26]. In an investigator-initiated first-in-human phase 1 benchmarking trial (*n* = 30), we previously reported safety and feasibility features of a topical DBD-generated NIPP-based prevention of acute RD [27]. In the follow-up phase 2 trial (*n* = 64), we established the preliminary efficacy of this approach, with a positive impact on both clinician- and patient-reported endpoints [28]. As expected, tolerability of NIPP was excellent and no side effects occurred.

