#### Non-invasive physical plasma

Several NIPP-generating devices are commercially available. The device used in this trial will be plasma care (terraplasma medical, Garching, Germany). This wireless, handheld, class 1 medical device is certified for use in the context of dermatological disorders, specifically for prophylaxis and therapy of inflammatory skin diseases caused by ionising radiation. In this setting, it can also explicitly be used as an add-on to standard skin care. The device is used with a separate sterile spacer with a 4 × 4 cm NIPP contact surface. For each patient and each visit, the device is then pressed loosely onto the patient’s breast skin, ensuring that the distance to the skin is always kept the same (Fig. 1). The application will be repeated in each of the breast quadrants. Based on the initial feasibility and dose-escalation trial, the daily treatment time is set at 120 s, using the device’s preset programme to ensure a constant dose of NIPP [27]. NIPP will be applied daily by a trained radiation oncology nurse, following every radiation fraction.

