## Discussion

RD remains the most common acute side effect of breast irradiation and radiotherapy in general. Progress in the development of new prophylactic and therapeutic agents has been slow, leading to a considerable physical and psychological impact on numerous patients. While topical corticosteroids are effective in reducing RD-related symptoms, their widespread and prolonged use remains limited due to the associated side effect profile [42, 43]. Care should be taken especially if moist desquamation is present, as topical corticosteroids might delay wound healing or even promote infection.

Trials investigating new ways to prevent or treat RD often recruit heterogeneous patient collectives in terms of dose-fractionation regimens and treatment sites, with the majority lacking a uniform control group or adequate placebo control. Another issue is the subjectivity of physician-assessed RD gradings such as CTCAE or RTOG, the most common primary endpoints, with considerable inter- and intra-observer variability and significant discrepancies with the patient’s perspective [44]. To accurately investigate prevention and treatment strategies, there is a need for sufficiently powered randomised controlled trial, recruiting a homogeneous patient collective in terms of RD risk, with a robust design (including CRO, PRO, and objective assessments) and apt placebo control, as is the case in this proposed trial protocol.

If the trial results in breast cancer patients are promising, the beneficial effects and lack of side effects of NIPP could potentially be translated to other patients and treatment sites at-risk for developing RD, e.g. those receiving radiotherapy for head and neck or skin cancer, or even accidental radiation injuries of the skin [45]. Adjuvant breast irradiation is chosen as the primary setting to investigate the use of NIPP in this trial due to its high prevalence, homogeneous treatment sites and radiation dose-fractionation concepts.

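### Adverse-event reporting is ruled out because earlier trials saw no events, but zero events cannot confirm absence, and no means is stated to record serious, unexpected, non-breast or device-related events by arm

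*Protocol article*

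**What the plan says.** Under Adverse event reporting and harms {22} the article gives this answer: "Not applicable. In both initial trials, no adverse events were reported, in line with previous trials using NIPP for other skin disorders". The sentence ends by treating that record as "confirming the complete absence of side effects".

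The size of the sponsor's own evidence is in Background and rationale {6a}: a "first-in-human phase 1 benchmarking trial (*n* = 30") and then "In the follow-up phase 2 trial (*n* = 64"), with the remark "As expected, tolerability of NIPP was excellent and no side effects occurred". The same section cites several other NIPP trials on safety, without patient numbers, and qualifies their finding as holding up to now.

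The same reasoning appears in Interim analyses {21b}: "The excellent safety profile of NIPP renders an interim safety analysis or stopping rules obsolete". The Discussion says that, should the results be promising, "the beneficial effects and lack of side effects of NIPP could potentially be translated to other patients".

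The article does collect local outcomes in both arms:
- **Clinician-reported:** weekly, end-of-treatment, 2-week and 6-week dermatitis grading by a blinded oncologist, with hyperpigmentation, oedema, desquamation and corticosteroid prescriptions.
- **Patient-reported:** pain, itching, burning and limitation of daily activities, at the end of treatment and at both follow-up visits.
- **Objective:** spectrophotometer readings.
- **Other:** medication for local symptoms, reasons for withdrawal, and a yes/no exit questionnaire.

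**The concern.** A condensed article may leave the detail of harms collection to the full protocol. This one does not leave the matter open. It takes the position that adverse-event reporting does not apply, and it gives a reason. If the reason is wrong, the position has no support.

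Two things are at stake. First, a serious or unexpected event, or one caused by the device, has no stated means of being recorded by arm. Second, the trial could end with a statement about absent side effects that its data cannot carry, because the relevant events were not systematically recorded. Events not recorded during treatment are hard to recover afterwards.

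**Working it through.** **Inputs**
- Earlier patients: 30 (phase 1) and 64 (phase 2), from Background and rationale {6a}. Sum: 30 + 64 = 94.
- Events: 0, from the same section.
- Present trial: 140 analysed (70 per arm) and 168 randomised (84 per arm at 1:1), from Sample size {14}.

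The article states no adverse-event rate or bound to reproduce. Its sample size matters here only for the number exposed. With a difference of 0.35, SD 0.7, 80% power and two-sided 5%, the exact t-test gives 63.77, so 64 per arm and 128 in all, as stated. Then 128 × 1.1 = 140.8 (stated: 140) and 140 × 1.2 = 168 (as stated). Whether multiplying by 1.2 is the right drop-out adjustment is a separate matter.

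**What zero events allow**

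The exact binomial upper bound after 0 events in n patients is 1 − 0.05^(1/n) (one-sided 95%) or 1 − 0.025^(1/n) (two-sided 95%).

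| Patients, 0 events | One-sided 95% | Two-sided 95% |
|---|---|---|
| 30 | 9.5% | 11.6% |
| 64 | 4.6% | 5.6% |
| 94 | 3.1% | 3.8% |

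The probability of seeing nothing in 94 patients is (1 − p)^94. At an assumed true rate of 1% it is 0.99^94 = 39%; at 2% it is 0.98^94 = 15%. An event-free record is thus unremarkable for a device with a real, low event rate.

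The figure of 94 is an upper limit. The intervention section says: "Based on the initial feasibility and dose-escalation trial, the daily treatment time is set at 120 s". Phase 1 therefore varied the exposure, and fewer than 94 patients may have had the present one. Background and rationale {6a} also puts dermatitis at up to 85% of patients, so an earlier trial in irradiated patients with no adverse events can only mean none attributed to NIPP.

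**What this trial could add if events were recorded**

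The chance of at least one NIPP-arm event is 1 − (1 − p)^n. The rates are assumptions for illustration.

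| True rate p | n = 70 | n = 84 |
|---|---|---|
| 1% | 51% | 57% |
| 2% | 76% | 82% |
| 5% | 97% | 99% |

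Zero NIPP-arm events would give a one-sided bound of 1 − 0.05^(1/70) = 4.2% or 1 − 0.05^(1/84) = 3.5%. Pooled with the earlier 94 patients, the bound would be 1.8% (164 patients) or 1.7% (178). Without recording, the trial adds nothing to the bound for events outside its listed outcomes.

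**What has no stated capture**

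Outcomes {12} covers the breast skin and four breast-related items. The concomitant-care section says other radiotherapy toxicities will be treated; it does not say they will be recorded. The blinding section keeps the device operator, who is present at every application, out of all assessments, so an event at application has no stated way onto a form. Emergency unblinding envelopes are provided, but no rule for recording the emergency.

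**The case against.** The strongest reply is that the likely harms of a topical skin device are local, and that these are sought at every visit by a blinded assessor in both arms. The sample size is two-tailed and no one-sided test is specified. This stands. A reader might infer from the words not applicable that the trial cannot detect harm at all, or that no harms are sought. The documents do not support that: more dermatitis, desquamation, pain, itching or burning under NIPP could appear. The gap is limited to serious, unexpected and non-breast events, and to events attributed to the device.

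Four further points narrow the matter:
- **The evidence cited is wider than 94 patients.** It includes NIPP trials elsewhere, and the device is described as class 1 and certified for radiation-induced skin inflammation. The 3.1% and 3.8% bounds therefore describe the sponsor's own two trials only. The other trials come without numbers and, in the harms section, concern other skin disorders. More event-free patients would tighten the bound but could not bring it to zero.
- **Some oversight exists.** There are emergency envelopes, five investigator meetings and yearly monitoring under a manual not shown. One may say that no reporting route is stated, but not that none exists.
- **The Discussion is conditional.** It speculates about extending a lack of side effects; it does not plan to do so.
- **Novelty cannot be claimed.** One might infer that this is the programme's first parallel-group sham comparison. The article implies a within-breast design for phase 2 but does not describe phase 1 well enough to say so.

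The absence of an interim safety analysis or stopping rule is not contested here. Only the reason given for it shares the faulty inference.

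**Conclusion.** The point holds in limited form. The article declares adverse-event reporting not applicable because it treats an event-free record as proof of absence. At most 94 event-free patients leave room for a true rate of up to 3.1% (one-sided) or 3.8% (two-sided), and more if fewer had the present exposure. Beyond the prespecified skin and symptom outcomes, no means is stated to record serious, unexpected, non-breast or device-attributed events by arm. The trial could not then support a general statement that side effects are lacking.

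The primary efficacy comparison is unaffected. The bounds assume that all 94 patients were exposed and observed, and that none had an event attributed to the device. The range of 4.2% to 3.5% for this trial depends on whether 70 or 84 NIPP patients are treated and followed. The point should be fixed, because it bears on participant protection and on a conclusion that the article already has in view.

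**What to change.** Replace the answer under {22} with a rule:
- At each existing weekly, end-of-treatment, 2-week and 6-week visit, the blinded investigator records adverse events with grade, seriousness and relation to the device, from the first application to the 6-week visit.
- The device operator logs events seen at application on a separate form that does not reveal the allocation to the assessor.
- Serious and device-related events are reported to the sponsor.
- Events are tabulated by arm for all treated patients, with exact confidence intervals.

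Reword the claim of confirmed absence to say that no side effects have been observed so far, and align the reasoning in Interim analyses {21b} with it. Limit any safety conclusion, including the one foreshadowed in the Discussion, to the events actually collected.

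The cost is one extra form page per visit and a short amendment through the route that the article already describes. No extra visits are needed. Patients enrolled before the change would lack prospective records, so the report should state from which date events were collected.
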